**Methods/design:**

This is a randomized controlled trial. Participants will be recruited from a public emergency department at Restinga district in Porto Alegre, southern Brazil. A total of 380 patients will be randomly assigned into 2 groups at the moment of emergency department discharge after receiving medical orientations: an intervention group, consisting of a structured individual counseling session by a pharmacist in addition to written orientations, or a control group, consisting only of written information about the disease. Outcomes will be assessed in an ambulatory visit 2 months after the randomization. The primary outcome is the proportion of patients with high medication adherence assessed using the Morisky-Green Test and the Brief Medication Questionnaire. The secondary outcomes are reduction of blood pressure, glycated hemoglobin, fasting plasma glucose, quality of life and number of visits to the emergency department.

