### Baseline measures

Data collection at baseline includes measurement of BP (for patients with hypertension), glycated hemoglobin (HbA1c) and fasting plasma glucose (for patients with diabetes). In addition, medication in use, socio-demographic, comorbidity and anthropometrical variables (for example, gender, age, ethnicity, marital and smoking status, alcohol consumption, physical activity, circumferences and body mass index) will be recorded. The medical prescription at discharge will also be documented.

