### Secondary endpoints

The secondary outcomes are:systolic and diastolic BP, for patients with diagnosis of hypertension;HbA1c and fasting plasma glucose, for patients with diagnosis of diabetes;quality of life, assessed by the the EuroQol five-dimension (EQ-5D) instrument [23,24];number of visits to the ED.

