### Data analysis

The questionnaires will be entered into the database through processing by optical reader, using the Remark Office OMR® Software (version 8.0 Gravic, Inc., Malvern, PA) . All analyses will follow the intention-to-treat (ITT) principle. For the primary outcome, we will initially consider in the analysis patients with complete follow-up. A secondary analysis will be performed with data of all patients initially randomized, considering, as the worst plausible scenario, that 29% of the losses to follow-up, in both groups, are adherent. The worst plausible scenario was based on a previous observational study, conducted in 2012 in the same region, showing that 34.5% (95% confidence intervals (CI), 29% to 40%) of patients with hypertension assisted in basic health units are adherent according to the same instrument [26]. We will not use any imputation method for continuous outcomes, such as BP and blood glucose. For these outcomes, we will include only those participants who attended the follow-up visit.

Data will be presented as relative risk (RR) and mean difference (MD), with 95% CI. Categorical variables will be compared using the chi-square test; continuous variables will be compared using the Student *t-*test or the Mann–Whitney *U-*test. The analysis will be conducted in SPSS for Windows (version 19.0, Redmond, WA, USA) and Stata (version 10, College Station, TX, USA); the statistician will be blinded for the randomization status.

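### BP, HbA1c and fasting glucose are compared by unadjusted t-test or Mann-Whitney although their baseline values are measured: valid, but it gives up precision, and a Mann-Whitney p-value does not match the reported mean difference.

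*Protocol article*

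**What the plan says.** All references are to the protocol article.

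- **Data analysis** names the tests: "continuous variables will be compared using the Student" t-test or the Mann-Whitney U-test. No covariate or model is named.
- **Data analysis** also fixes the effect measure: "Data will be presented as relative risk (RR) and mean difference (MD), with 95% CI". For the continuous outcomes the analysis set is follow-up attenders: "For these outcomes, we will include only those participants who attended the follow-up visit".
- **Baseline measures** shows that the covariates exist: "Data collection at baseline includes measurement of BP (for patients with hypertension), glycated hemoglobin (HbA1c) and fasting plasma glucose (for patients with diabetes".
- **Secondary endpoints** lists values, with no mention of change: "systolic and diastolic BP, for patients with diagnosis of hypertension" and "HbA1c and fasting plasma glucose, for patients with diagnosis of diabetes".
- **Abstract, Methods/design** uses different wording: "The secondary outcomes are reduction of blood pressure, glycated hemoglobin, fasting plasma glucose, quality of life and number of visits to the emergency department".
- **Randomization and participants allocation** stratifies 1:1 allocation by number of medications (fewer than five, or five or more). Baseline BP and glycaemia are not stratification factors.

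**The concern.** The trial measures BP, HbA1c and fasting glucose in the relevant patients before randomization, then specifies tests that cannot use those values as covariates. Randomization does not balance them by design either, since the only stratifier is medication count. A chance difference between arms in baseline BP or glycaemia would therefore carry through to the 2-month comparison.

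The Discussion hypothesizes that better adherence will lead to better BP and glycaemic control, and these outcomes carry that part of the hypothesis. BP is analysed only in patients with hypertension and glycaemia only in patients with diabetes, so each analysis may have fewer patients than the trial as a whole. Precision is worth keeping here.

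There is also a mismatch between test and estimate. The plan reports a mean difference, but Mann-Whitney does not test a difference in means. If it is used, the p-value and the confidence interval answer different questions and can disagree.

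**Working it through.** **1. The plan's own figure.** The Sample size section uses 50% against 65% adherence, two-sided 5%, 80% power and 10% losses. With the pooled formula, n = [1.96·√(2·0.575·0.425) + 0.842·√(0.25 + 0.2275)]² / 0.15², which rounds up to 170 per arm. Then 170/0.9 = 189, against 190 stated. The figure reproduces, and this point does not touch it. Expected attenders are 190 × 0.9 = 171 per arm.

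**2. Inputs not in the article.** No standard deviation (SD) and no baseline-to-follow-up correlation r is given. Differences are therefore in units of the follow-up SD, and r is assumed at 0.3, 0.5 and 0.7.

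**3. Variance.** In large samples, the variance of the adjusted treatment difference relative to the unadjusted 2-month difference is 1 − r². This assumes a similar linear relation in both arms. It does not require equal SDs at the two visits. The sample size an unadjusted analysis would need for the same precision is 171/(1 − r²).

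**4. Detectable difference and power.** Unadjusted, at 80% power: (1.96 + 0.842)·√(2/171) = 0.303 SD. With ANCOVA this is multiplied by √(1 − r²). The power column is for ANCOVA at a true difference of 0.303 SD.

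| Assumed r | Relative variance 1 − r² | Detectable difference (SD) | Power at 0.303 SD | Unadjusted n per arm to match |
|---|---|---|---|---|
| none (unadjusted) | 1.00 | 0.303 | 80% | 171 |
| 0.3 | 0.91 | 0.289 | 83.6% | 188 |
| 0.5 | 0.75 | 0.262 | 89.9% | 228 |
| 0.7 | 0.51 | 0.216 | 97.5% | 335 |

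The last column is 10%, 33% and 96% above 171.

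**5. Diagnosis subsets.** The article does not give the share of patients with each diagnosis. At an assumed 50% share (about 86 per arm), the unadjusted detectable difference is 2.802·√(2/86) = 0.43 SD. With ANCOVA at r = 0.5 it is 0.428 × √0.75 = 0.37 SD.

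**6. Chance imbalance.** With 171 per arm, the baseline difference between arms has a standard error of √(2/171) = 0.108 baseline SD, so 95% of randomizations fall within ±1.96 × 0.108 = ±0.21 SD. Given an imbalance of that size, the unadjusted 2-month difference is shifted by r × 0.21, or about 0.11 follow-up SD at r = 0.5. Over all randomizations the shift averages to zero. In any one trial, ANCOVA removes it and the named tests do not.

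**7. Test against estimate.** Mann-Whitney tests whether values in one arm tend to exceed those in the other. The interval reported is for a difference in means. With skewed values such as glucose, the interval can exclude zero while the p-value is above 0.05, or the reverse.

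**The case against.** **The comparison is valid.** Under 1:1 randomization the unadjusted difference in 2-month values is unbiased and its test is sound. This stands in full: the point concerns efficiency, not error.

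**Detail may sit elsewhere.** A condensed article can leave adjusted models to a fuller protocol or analysis plan, and the sentence on tests is a generic one covering all variables. This softens the point but does not remove it. The article positively names the unadjusted tests and mentions no model, so a reader would take them as the plan.

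**The gain may be small for BP.** Many patients enter on a high emergency-department BP, which may weaken its correlation with the 2-month value. This also stands. At r = 0.3 the gain is worth only 10% more patients, and 96% should not be read as the expected figure.

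Four stronger readings are tempting but unsupported:

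- *The outcome definition is contradictory, so change scores may be planned.* The Abstract's word *reduction* also governs quality of life in the same sentence, and a reduction in quality of life cannot be the aim. It reads as loose shorthand for the hoped-for direction. Secondary endpoints is the operative list, and it gives values.
- *Entry thresholds select all these baselines, so change scores would be worse than levels.* The thresholds in Inclusion criteria apply to BP and capillary glucose. HbA1c and fasting plasma glucose have none, and a patient with hypertension may qualify on glucose alone. The size of any change-score penalty also depends on k, the ratio of baseline to follow-up SD, through 1 + k² − 2rk. At r = 0.3 this is 1.40 for k = 1 but 1 + 0.49 − 0.42 = 1.07 for k = 0.7. The article gives neither r nor k.
- *These are the only objective outcomes.* Number of emergency visits is also listed, and nothing says that it is self-reported.
- *The emergency-visit analysis needs a different model on the same grounds.* The baseline argument says nothing about that outcome. Nor does it extend to EQ-5D, which Baseline measures does not list.

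**Conclusion.** The point holds as a precision improvement for BP, HbA1c and fasting plasma glucose, together with the mismatch between a Mann-Whitney p-value and a reported mean difference. It does not show bias or an invalid test. It leaves the primary adherence outcome and the 190 per group unchanged.

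The direction is secure: in large samples, ANCOVA on baseline is at least as precise as an unadjusted comparison of 2-month values whatever r is. The size is not secure. It is a 9% to 49% reduction in variance over r = 0.3 to 0.7, and those r values are assumptions. The Mann-Whitney mismatch arises only if that test is used, but the plan allows it. The difference in wording between the Abstract and Secondary endpoints needs tidying and is not a defect in its own right.

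**What to change.** 1. In **Secondary endpoints**, state that BP, HbA1c and fasting plasma glucose are the values at the 2-month visit. Change the Abstract's *reduction* wording to agree.
2. In **Data analysis**, replace the choice between t-test and Mann-Whitney for these outcomes with ANCOVA: 2-month value on arm, baseline value of the same measure, and medication-count stratum. Report the adjusted mean difference with its 95% CI and p-value from that one model, using robust standard errors so that skewness or unequal variance does not prompt a switch of test.
3. Fix this before allocation is unblinded.

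The cost is a few sentences. The baseline values and the stratum are already recorded, so no extra visits, measurements or patients are needed, and the sample size stays as it is.

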### Ethics

This study has been approved by the Institutional Review Board of Hospital Moinhos de Vento of Porto Alegre (approval number 403.658). Written informed consent will be obtained from each participant at the time of enrolment. The trial has also been registered in the Clinical Trial Registry NCT01978925 and in the Brazilian Registry of Clinical Trials U1111-1149-8922, and according to the Brazilian Ethics in Human Research Regulations.

## Discussion

We present a study protocol for a randomized controlled trial to investigate the impact of pharmaceutical care in patients with chronic conditions at discharge from an ED. The study will be conducted in a setting with social vulnerability in a developing country. We already knew that at least half of the people in treatment for hypertension and/or diabetes in the same community do not adhere adequately to medications. As consequence, many would develop undesirable outcomes, such as clinical complications and increase in the use of health services resources that could be avoided with adequate adherence to the medical prescription. The moment of the discharge from the ED may constitute an important opportunity for medication reconciliation, reviewing and providing information related to the medications of continuous use [27,28]. In this context, we are proposing an intervention focused on pharmaceutical care at emergency discharge in order to enhance adequate medication use. Our hypothesis is that patients receiving pharmaceutical orientation in the intervention group will present better adherence to pharmacological therapy, resulting in better control of BP and glycemic profile in our study population.

Several studies have shown that pharmaceutical care in the treatment of patients with hypertension and diabetes has been associated with significant reductions in hospitalizations, visits to the ED and increase in medication adherence [3,9,17-19]. These studies were conducted mainly in hospital and ambulatory settings in developed countries. To our knowledge, this study is the first designed to evaluate the effectiveness of pharmaceutical care interventions in patients discharged from a public ED. With this randomized controlled trial we expect to provide evidence regarding the effectiveness of pharmaceutical care for chronic conditions at ED discharge. As consequence, these results may be useful for policy -making related to the development and implementation of pharmaceutical care programs in emergency services.

## Trial status

The trial is currently in the recruitment phase.

## Abbreviations

BMQ: Brief Medication Questionnaire
BP: blood pressure
CI: confidence interval
CVD: cardiovascular disease
DALY: disability-adjusted life year
ED: emergency department
EQ-5D: EuroQol five-dimension instrument
HbA1c: glycated hemoglobin
HDI: Human Development Index
ITT: intention-to-treat
MD: mean difference
MGT: Morisky-Green Test
RA: research assistant
RR: relative risk
